#### 8.4.4 Recording and Reporting of Adverse Events

Researchers should meticulously document any adverse events that occur in the subjects, including: a description of the adverse event and all related symptoms, the time of occurrence, severity, end time, measures taken, and the final outcome.

From the time the subject signs the informed consent form until 28 days after the last dose, drug safety assessments are required. All adverse events (both serious and non-serious) should be recorded on the adverse event reporting page of the case report form, using precise medical terminology. Follow-up should continue until the adverse event returns to Grade I or below, or until the investigator deems further follow-up unnecessary (e.g., clinical stability is achieved).

## **8.5 Serious Adverse Events (SAEs)**

### **8.5.1 Definition of Serious Adverse Events**

A serious adverse event (SAE) is any medical event occurring during a clinical trial that requires hospitalization, prolongs hospital stay, results in disability, affects work capacity, is life-threatening, or leads to death, or causes congenital anomalies. Adverse events meeting one or more of the following criteria are considered SAEs:

- Resulting in death;
- Life-threatening (defined as an immediate risk of death at the time of the event);
- Requiring hospitalization or prolonging hospital stay;
- Causing permanent or significant disability/functional impairment;
- Resulting in congenital anomalies or birth defects;
- Important medical events: These adverse events may not be life-threatening, but based on medical judgment, they may endanger the subject and require medical or surgical intervention to prevent any of the above outcomes.

Investigators should promptly report all SAEs, including clinical diagnosis, treatment, and outcomes, and follow up until the event is resolved, alleviated, or stabilized. Detailed records should be maintained in the original medical records and eCRF forms (including the adverse event report form; if death occurs, a death report form should be completed), and an SAE report form should be filed.

### **8.5.2 Tumor Disease Progression**

Tumor disease progression is defined as the deterioration of the subject's condition due to tumor disease progression, including radiological progression and the progression of clinical symptoms and signs. The appearance of new metastatic sites of the primary tumor or the progression of existing metastatic sites is considered disease progression. Events that are life-threatening, require hospitalization or prolong hospital

stay, or result in permanent or significant disability/functional impairment, congenital anomalies, or birth defects due to symptoms and signs of disease progression are not reported as SAEs. If there is any uncertainty about whether an SAE is due to disease progression, it should be reported as an SAE.

## **8.6 Research-Related Injury and Compensation**

While this study will be conducted in strict compliance with applicable laws and regulations, adverse reactions may still occur. In the event of research-related injury, the investigator will provide immediate medical care and treatment. Compensation for damages will be provided in accordance with legal requirements if negligence is determined. The investigator will make every effort to prevent and manage any potential harm resulting from study participation.

## **9 Management of the Research Project**

### **9.1 Ethical Standards and Informed Consent**

#### **9.1.1 Ethical Standards**

This clinical trial must adhere to the Declaration of Helsinki, the "Good Clinical Practice" (GCP) guidelines issued by the NMPA, and relevant regulations. Before the start of the trial, approval from the hospital's ethics committee must be obtained. Any modifications to the trial protocol during the clinical research must be reported to the ethics committee for record-keeping. Investigators are responsible for submitting interim reports to the ethics committee in accordance with their requirements and informing them of the trial's conclusion.

#### **9.1.2 Informed Consent**

Subjects must provide informed consent before participating in this observational study. Participants may optionally consent to future use of de-identified data for CINV-

related research, with separate approval required for new studies.

## **9.2 Drug Management**

The drugs used in this study are already marketed in clinical practice, and no other medications are provided.

## **9.3 Protocol Amendments**

No one other than the sponsor is permitted to amend the protocol. Any necessary changes must be made in the form of protocol revisions and submitted to the ethics committee for approval or record-keeping after obtaining signatures from the sponsor and the principal investigator. All modifications must be detailed in the protocol.

## **9.4 Monitoring**

The sponsor appoints personnel with appropriate medical, pharmaceutical, or related academic qualifications, who have undergone necessary training and are familiar with GCP and relevant regulations, to oversee the collection of information for this clinical trial. They ensure that trial records and reports are accurate, complete, and error-free, and that the trial adheres to the approved protocol, GCP, and relevant regulations. Monitoring of adverse events and serious adverse events in clinical trials ensures that all such events are accurately, reliably, and promptly recorded and reported.

## **9.5 Quality Control and Assurance**

Clinical research units must be designated by the NMPA as qualified for clinical research.

## **9.6 Data Management**

### **9.6.1 Data Collection**

This study employs eCRF for the collection of research data.

### **9.6.2 Data Management and Quality Control**

All participant data will be de-identified using unique codes, stored in password-protected systems, and accessible only to authorized study personnel. Identifiable information will not be shared externally without separate participant consent, except as required by regulatory authorities. Data will be retained for 5 years post-trial completion before secure destruction. To ensure the authenticity and reliability of clinical trial data and enhance data quality, clinical monitors will follow standard operating procedures to review the completeness, consistency, and accuracy of trial data in the clinical database during the project. They will guide research institution staff in supplementing or correcting problematic data as necessary. At the end of the trial, data managers and medical personnel will conduct a final quality control review of all database data, summarizing all protocol deviations and violations that occurred during the trial. Once the data in the database meet quality requirements, the database will be locked, and data managers will export the data for statistical analysis by the statistics department.

### **9.6.3 Data Review**

Investigators must retain the original files of each patient participating in the trial, including study medical records and visit records (inpatient or outpatient medical records), which include demographic and medical information, laboratory data, electrocardiograms, and results of any other tests or evaluations. All information on the eCRF must originate from the original files in the patient's records. Investigators must also retain the informed consent forms signed by the patients.

## **9.7 Protocol Deviations**

All requirements specified in the study protocol must be strictly followed. Any intentional or unintentional deviations from or violations of the trial protocol and GCP principles are classified as protocol deviations or violations.

## **9.8 Publication of Study Results**

All articles and reports related to the trial must be approved by the investigators before publication.

# **10 Data Analysis and Statistical Methods**

## **10.1 Sample Size Estimation**

Based on previous studies of 8-12 mg DEX plus NEPA for CINV prevention [8,10], a CRR of 80% was assumed for the control group (8D DEX group). The non-inferiority margin was set at 15%. For the sample size calculation, the CRR in the experimental group (5D DEX group) was also assumed to be 80% under the null hypothesis of non-inferiority. Using a normal approximation method for non-inferiority testing of proportions (Z-test, unpooled, one-sided  $\alpha=0.05$ , power=80%), a total of 176 participants (88 per group) was calculated to be sufficient to demonstrate non-inferiority. To account for a potential 5% attrition rate, the enrollment was increased to 186 participants (93 per group). The sample size calculation was performed using PASS 2021 software.

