| Sample Size Calculation           | 186 subjects                                                                                                                                                                                                                                                                                                                                                                                                                                                                                                                                                                                                                                                                                                                                                                                                                                                       |
| Data Analysis/Statistical Methods | 
 
• Intention-To-Treat (ITT): Includes all randomized subjects, regardless of whether they completed the study, deviated from the protocol, or dropped out.
 
• Modified Intention-To-Treat (mITT): mITT is a variation of ITT that excludes certain participants post-randomization based on predefined criteria (e.g., major protocol violations, ineligibility, or lack of any post-baseline data).
 
• Per Protocol Set (PPS): includes only participants who fully adhered to the trial protocol (e.g., completed treatment, complied with visits, and had no major violations).
 
• All statistical analyses will be performed using SPSS 26.0 statistical software and RStudio v4.3.3. All statistical tests will be two-sided, with a significance level of <math>P \leq 0.05</math>.
 
 |

|                       |                                                                                                                                                                                                          |
|-----------------------|----------------------------------------------------------------------------------------------------------------------------------------------------------------------------------------------------------|
| Study Timeline | 

• First subject enrollment: October 2024

• Estimated last subject enrollment: August 2025

• Estimated study completion date: August 2025

 |

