### 10.5 General Principles for Efficacy Analysis

In this study, unless otherwise specified, efficacy data will be descriptively summarized according to the following general principles:

- Demographic and clinical characteristics were analyzed using descriptive statistics, with categorical variables expressed as frequencies (percentages) and continuous variables as median (interquartile range).

- The efficacy endpoints (CRR, TCR, and CCR) were analyzed for noninferiority using a stratified Mantel-Haenszel approach to compare dose cohorts, adjusting for age. The combined risk difference and its two-sided 95% confidence interval were calculated. Noninferiority was concluded if the lower confidence limit exceeded the pre-specified margin of -15%. Changes in response within subjects across different treatment phases were assessed using McNemar's test. P values for noninferiority tests were reported as one sided, whereas other P values were two sided.
- Group comparisons employed chi-square/Fisher's exact tests for binary variables, Mann-Whitney U test for continuous variables, and Kruskal-Wallis test for multicategorical data.

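### The 80% power in section 10.1 is computed at one-sided alpha 0.05, but section 10.5 decides on a two-sided 95% interval; under that rule power is about 70 to 73%

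*Protocol*

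**What the plan says.** Section 10.1 of the protocol gives the method as "Using a normal approximation method for non-inferiority testing of proportions (Z-test, unpooled, one-sided" and the error rates as "one-sided $\alpha=0.05$ , power=80" percent. For the reference arm, "a CRR of 80% was assumed for the control group (8D DEX group"), and "the CRR in the experimental group (5D DEX group) was also assumed to be 80" percent. The margin is 15 percentage points. The conclusion is that "a total of 176 participants (88 per group) was calculated to be sufficient to demonstrate non-inferiority", raised to 186 (93 per group) for 5% attrition.

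Section 10.5 sets the analysis of complete response as an age-stratified Mantel-Haenszel comparison: "The combined risk difference and its two-sided 95% confidence interval were calculated". Non-inferiority is concluded when the lower limit of that interval lies above -15%. The section adds that "P values for noninferiority tests were reported as one sided, whereas other P values were two sided", and gives no threshold for the one-sided P value.

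The Data Analysis/Statistical Methods row of the Protocol Synopsis has a general sentence: "All statistical tests will be two-sided, with a significance level of" 0.05.

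**The concern.** The lower limit of a two-sided 95% interval leaves 2.5% in the tail, so requiring it to clear the margin is a one-sided test at 0.025. A one-sided 0.05 calculation corresponds to a two-sided 90% interval, which the protocol does not mention. Sections 10.1 and 10.5 therefore describe two different tests of the same hypothesis, and the power in the first does not belong to the decision in the second.

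What is at stake is the chance that the trial fails to show non-inferiority when the two doses really are equally effective. Section 10.1 implies that this chance is 20%. If it is materially larger, an inconclusive result becomes more likely than planned, and anyone reading such a result would be relying on a power figure that the design does not have.

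**Working it through.** **Inputs.** All are from section 10.1 unless noted.
- Response rate: 0.80 in each arm, so the true difference is 0.
- Margin: 0.15.
- Test: unpooled Z-test, one-sided alpha 0.05, power 80%.
- Patients per group: 88 evaluable, 93 enrolled.
- Decision rule, from section 10.5: lower limit of the two-sided 95% interval above -0.15, so the normal quantile is 1.960 rather than 1.645.

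**Step 1: reproduce the protocol's figure.**

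n per group = (z_alpha + z_power)² × [0.8×0.2 + 0.8×0.2] / 0.15²

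At one-sided 0.05: (1.645 + 0.842)² × 0.32 / 0.0225 = 87.93, so 88 per group and 176 in total. With 5% attrition, 176 / 0.95 = 185.3, so 186. Both figures match section 10.1, which confirms that one-sided 0.05 was used.

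**Step 2: power under the rule in section 10.5.**

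Power = Φ(0.15 / √(0.32/n) − z)

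- n = 88, z = 1.645: 80.0%. This is the stated figure.
- n = 88, z = 1.960: 0.15/0.0603 − 1.960 = 0.527, giving 70.1%.
- n = 93, z = 1.960: 0.15/0.0587 − 1.960 = 0.597, giving 72.5%.

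**Step 3: exact check.** The binomial probabilities were summed over all pairs of outcomes for which the unpooled lower limit exceeds -0.15.

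| Patients per group | One-sided 0.05 | One-sided 0.025 |
|---|---|---|
| 88 | 80.3% | 70.6% |
| 93 | 82.4% | 72.9% |

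The normal approximation is not the source of the gap.

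**Step 4: size needed for 80% power under the rule in section 10.5.**

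(1.960 + 0.842)² × 0.32 / 0.0225 = 111.6, so 112 per group and 224 evaluable. With 5% attrition, 224 / 0.95 = 235.8, so 236 enrolled.

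**Step 5: sensitivity to the response rate.** Section 1.2 reports a total complete response rate of approximately 85% in the team's earlier work. Putting 0.85 in both arms makes the variance term 2×0.85×0.15 = 0.255. Power under the 95% interval is then Φ(0.15/√(0.255/88) − 1.960) = 79.6% with 88 per group and 81.7% with 93.

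These calculations use the unstratified risk difference. Section 10.5 adjusts for age without defining the age strata, so I assume, rather than show, that stratification changes power little.

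**The case against.** **The arithmetic is right, and the stricter rule protects against false claims.** Both parts stand. The 88 follows from its inputs. The decision rule is tighter than the sizing alpha, so a positive result is held to a nominal 2.5%. Neither part rescues the 80%, which is attached to a test that the trial does not use for its conclusion.

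**A power of 70% is the pessimistic end.** This stands in part. The primary analysis set in section 10.3 is everyone enrolled who receives at least one treatment, and treatment is a single administration before chemotherapy. The analysed number may therefore be close to 93 per group, which gives 72 to 73%. If the true rate were 85% in both arms, power would be about 80% even under the 95% interval. The protocol chose 80% as its planning rate, however, so the shortfall holds under its own assumptions and should be stated as conditional on them.

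**A reader might infer that the protocol leaves open whether the P value or the interval decides.** It does not. Section 10.5 ties the conclusion to the confidence limit, and the one-sided P value is only reported. A clash arises only if 0.05 is carried over from section 10.1 as the threshold for that P value. In that case a one-sided P between 0.025 and 0.05 would look positive while the interval fails. By the exact calculation with equal true rates of 80%, this would happen in about 9.7% of trials with 88 per group (80.3 − 70.6) and 9.5% with 93 (82.4 − 72.9). That is a reason to state the threshold, not evidence that the rule is undecided.

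**A reader might also infer three conflicting alphas.** The synopsis level, two-sided 0.05, is the level of the two-sided 95% interval, so those two places agree and section 10.1 is the outlier. The synopsis sentence departs from section 10.5 only in not exempting the one-sided reporting of the non-inferiority P value.

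**Conclusion.** The point holds as an inconsistency between two sections that overstates planned power. With an 80% response rate in both arms and a 15-point margin, the rule that governs the primary conclusion has about 70% power with 88 evaluable per group and 72 to 73% with 93, not 80%. The chance of missing true non-inferiority is therefore about 27 to 30% rather than 20%. Reaching 80% would take 112 evaluable per group.

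The result depends on the 80% response rate, on equal true rates, and on age stratification having little effect. It does not mean that the sample size was miscalculated for its stated inputs, that type I error is inflated, or that the decision rule is ambiguous.

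**What to change.** Keep the two-sided 95% interval rule in section 10.5 and bring the other two places into line with it.

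- **Section 10.1:** replace one-sided alpha 0.05 with one-sided 0.025. State that, given an 80% complete response rate in both arms and a 15-point margin, power is about 70% with 88 evaluable per group and about 72 to 73% if all 93 per group are analysed.
- **Section 10.5:** state that the reported one-sided non-inferiority P value is read against 0.025 and that the interval decides.
- **Synopsis:** mark the non-inferiority P value as an exception to the sentence on two-sided tests.

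The cost is wording and a less favourable power statement; no extra patients are needed. If the sponsor wants to keep 80% power, the price is 236 enrolled instead of 186.

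Switching section 10.5 to a two-sided 90% interval would also make the sections agree, but it is not a wording change. It loosens the success criterion, and in an open-label trial it would need its own justification, fixed before any outcome data are seen. I do not recommend it as the repair.

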## **10.2 Randomization and masking**

Computer-generated randomization (SPSS v26.0) assigned 186 patients using a reproducible seed number (2000000). A sequence of random values ranging from 0 to 1 was generated for all 186 participants. Allocation was performed strictly in the order of this pre-generated sequence: the first 93 participants corresponding to the smallest

random values were assigned to the 5D DEX group, and the remaining 93 to the 8D DEX group. This sequential assignment based on a computer-generated random list ensured the randomness of allocation. Investigators enrolled eligible participants and allocated them according to this computer-generated randomization sequence. This open-label study maintained full allocation transparency to all investigators and participants throughout the single-cycle observation.

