## 4.2 Exclusion Criteria

Subjects with any of the following conditions are not eligible for this study:

1. Received radiotherapy within one week before chemotherapy.
2. Suffer from other diseases that cause nausea or vomiting except those caused by tumor chemotherapy drugs, including but not limited to gastrointestinal obstruction and central nervous system malignancies.
3. Experienced vomiting, nausea, or mild nausea within 24 hours before treatment.
4. Concurrent use of corticosteroids or any other possible antiemetic drugs.
5. Contraindications to corticosteroids.
6. Cognitive impairment (such as dementia or severe learning difficulties) that prevents completion of nausea and vomiting-related evaluation scales, etc.
7. Use of antipsychotic drugs within 30 days before the start of treatment or during treatment.
8. Severe and uncontrolled diseases affecting the liver, kidneys, cardiovascular, respiratory, endocrine systems, or the central nervous system.
9. Allergy to the study drugs.
10. Pregnant or lactating women.
11. Participated in any other clinical study of investigational drugs or devices within three months before screening.
12. The investigator deems that participation in the trial poses a significant risk to the subject's health or safety or may affect the assessment of efficacy for other reasons.

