## 6.1 Screening Phase

The screening phase begins with the signing of the informed consent form (ICF) by participants who meet the criteria of this study and ends with enrollment or screening failure. Participants who discontinue the study after signing the informed consent form but before enrollment will be considered as "screening failures."

The following screening steps must be completed within 14 days before starting the study drug treatment:

- Obtain written informed consent signed by the participant;

- Collect demographic information;

- Collect medical and treatment history;

- Collect medication history;

- Conduct physical examination and ECOG PS score;

- Laboratory tests, such as screening for infectious diseases, routine urinalysis, and stool examination;

- Collect relevant imaging results for tumor baseline assessment, such as chest and abdominal CT, brain MRI, bone ECT, etc.;

- Evaluate concomitant medications and treatments currently in use.

The following screening steps must be completed on the day of starting the study drug treatment:

- Physical examination, vital signs, and ECOG PS score;

- Laboratory tests, such as complete blood count, biochemical profile, coagulation function, etc.

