## 6.2 Treatment Phase

The treatment phase begins with the administration of the study drug and continues until the completion of this round of cancer treatment, disease progression, death, loss to follow-up, or initiation of new anti-cancer treatment, whichever occurs first. Participants should start receiving the study drug within 24 hours of enrollment.

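### Section 10.2 describes no allocation concealment and the flowchart permits randomisation before the last eligibility checks, so selection by known arm is possible and could bias the comparison in either direction

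*Protocol*

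**What the plan says.** **Who allocates.** Protocol 10.2: "Investigators enrolled eligible participants and allocated them according to this computer-generated randomization sequence". One list of 186 is generated in advance and split 93/93 by ranking random values. The program is named and the seed is printed ("using a reproducible seed number (2000000"). On the use of the list: "Allocation was performed strictly in the order of this pre-generated sequence". The section ends: "This open-label study maintained full allocation transparency to all investigators and participants throughout the single-cycle observation". Neither this section nor any other describes a central system, sealed envelopes, an independent list holder or stepwise release.

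**When.** The Study Flowchart ticks randomisation only in the screening column, D-3 to D0, to the left of Baseline D0. Section 6.1 has a second group of screening procedures: "The following screening steps must be completed on the day of starting the study drug treatment". They include physical examination, vital signs, ECOG score and "Laboratory tests, such as complete blood count, biochemical profile, coagulation function, etc". Exclusion 3 in 4.2 reads "Experienced vomiting, nausea, or mild nausea within 24 hours before treatment". Section 6.2 adds: "Participants should start receiving the study drug within 24 hours of enrollment".

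**Who is analysed.** Section 10.3 makes the mITT set primary and limits it to enrolled patients who received at least one treatment. The synopsis also defines an ITT set of all randomised subjects, but 10.3 does not use it. Section 10.5 adjusts the primary comparison for age only.

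**The concern.** Open-label treatment does not require open allocation. Concealment protects the moment of entry: whoever decides that a patient is eligible should not know the next arm. As 10.2 is written, the same people do both tasks from a fixed sequence and nothing hides the next entry from them. An investigator could defer or decline a patient according to the arm that comes next.

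The timing adds a second opening. If a patient is randomised on D-3, the arm is known while exclusion 3 and the treatment-day checks are still open. A patient ruled out at that point is never dosed and so leaves the primary analysis set.

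Section 1.3.1 itself notes that less dexamethasone may control CINV less well, so investigators may hold views about who should receive 5 mg. Adjustment for age would not correct an imbalance in emetic risk. What is at stake is the validity of the trial's only confirmatory comparison.

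**Working it through.** **1. The plan's own figure.** Inputs from 10.1: 80% in both arms, margin 15 points, one-sided alpha 0.05, power 80%, unpooled Z-test.

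n per arm = (1.645 + 0.842)² × (0.16 + 0.16) / 0.15² = 87.9, so 88 per arm and 176 in total. For 5% attrition, 176 / 0.95 = 185.3, so 186. The stated size reproduces. The concern is validity, and the fix leaves N alone.

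**2. Order of events.**

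| Step | Earliest or required time | Source |
|---|---|---|
| Randomisation | D-3 to D0 | Flowchart |
| Dosing | within 24 h of enrolment | 6.2 |
| Exclusion 3 | covers the 24 h before treatment | 4.2 |
| Examination, ECOG, blood count, biochemistry | treatment day | 6.1 |
| Entry to primary set | after dosing | 10.3 |

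Any randomisation before D0 precedes rows 3 to 5. D0 is inside the window, so this order is permitted and not required. The flowchart also ticks blood count and biochemistry at screening, and it does not tick blood count at Baseline D0, whereas 6.1 puts both on the treatment day.

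**3. What access to the list adds.** Someone who sees the list knows every next arm. Someone who does not, and guesses the arm with more places left in an unblocked 93/93 list, is right about 54% of the time (simulation, 5,000 lists). Access is the main problem.

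**4. Illustration of size.** The documents give no figure for selection, so these inputs are assumptions: half the patients high-risk and half low-risk, 8 mg response 70% and 90% respectively, and 5 mg truly 15 points lower in each class. Overall this is 80% v 65%, exactly at the margin. Non-inferiority is declared if the lower 95% limit exceeds -15% (10.5). The calculation is unstratified, with 93 per arm and exact binomial enumeration.

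- No selection: false non-inferiority 2.5%.
- 30% of high-risk patients deferred from 5 mg places and replaced: high-risk share = 0.5 × 0.7 / (0.5 × 0.7 + 0.5) = 0.412; 5 mg rate = 0.75 - 0.20 × 0.412 = 0.668; shift 1.8 points; **4.7%**.
- The same, plus the mirror image in 8 mg (high-risk share 0.588): 8 mg rate = 0.90 - 0.20 × 0.588 = 0.782; shift 3.5 points; **7.9%**.
- Reverse steering, with 5 mg at a high-risk share of 0.588: 5 mg rate 0.632; shift 1.8 points against 5 mg; **1.3%**. If the arms are truly equal at 80%, 5 mg is observed at 78.2% and power falls from **73% to 61%**.

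**5. Range.** With a bias favouring 5 mg of 2, 5 or 10 points, split equally between arms, false non-inferiority is 5.0%, 11.7% or 33.5%.

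**6. Loss before dosing.** At 65%, 93 patients give 60.45 expected responders. Removing 3 non-responders before dosing gives 60.45 / 90 = 67.2% (+2.2 points). Removing 5 gives 60.45 / 88 = 68.7% (+3.7 points).

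**The case against.** **The transparency sentence may describe only open-label treatment after assignment.** Read alone, it may. The point rests on the sentence before it, in which investigators enrol and allocate, and on the absence of any concealment step. Section 10.2 does not say who keeps the list or whether later entries are visible, so a reader should not infer that investigators are shown to hold it. The plan simply does not prevent it.

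**The timing is not fixed.** This stands. D0 randomisation is allowed, dosing must follow enrolment within 24 hours, and the screening blood tests could settle inclusion 5 before assignment. A reader might infer that the last checks always come after randomisation. The documents support only that they may.

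**The direction is not known.** This also stands. A reader might infer that selection must favour non-inferiority. Nothing in the documents says which way investigators would steer, and steering against 5 mg costs power.

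**The printed seed does not by itself open the list.** Agreed. Rebuilding it also needs the exact SPSS procedure. The seed is a secondary route.

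**The allocation wording might be read as giving 5 mg to the first 93 patients enrolled.** The text ties the split to the smallest random values, so that reading is not well supported.

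**The figures are assumed.** They are. At the one-sided 0.05 level used for the sample size, the two-way case gives 13.8%, to be compared with 5.1% and not with 2.5%. The decision rule in 10.5 uses the 95% interval.

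**Conclusion.** The point holds as a gap in design. Section 10.2 describes no concealment, the people who judge eligibility also allocate, the flowchart permits randomisation before the final checks, and the primary set omits anyone not dosed. Selection by known arm is possible, and the age-adjusted analysis would not repair it.

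Its size cannot be taken from the documents. On the assumed risk mix and 30% deferral, false non-inferiority at a true 15-point deficit runs from 1.3% to 7.9% around a nominal 2.5%, depending on direction and on whether one or both arms are steered. The documents do not support a claim that selection has occurred, that it would favour 5 mg, or that every patient is randomised before the last check. The matter should still be fixed before the result is relied on, because concealment cannot be restored by analysis and is cheap to provide.

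**What to change.** 1. **Section 10.2.** Replace the allocation text: a list made with a new, unpublished seed is held in the EDC the trial already uses; enrolling investigators have no access to the list or seed; each assignment is tied to the enrolment number and released one at a time, only after all eligibility checks, including those on the treatment day, are locked.
2. **Flowchart.** Move the randomisation tick to D0, after those checks, and reconcile the blood-count timing with 6.1.
3. **Section 10.3 and reporting.** Report every randomised patient by arm, with reasons for non-dosing, and add an analysis of the all-randomised ITT set already defined in the synopsis.
4. **Blocking** is not needed for concealment. In an open-label, single-centre trial, known or guessable blocks make assignments easier to predict. If blocks are used, their sizes should vary and stay undisclosed.
5. **If enrolment has begun.** Section 10.2 is written in the past tense and the timeline starts in October 2024, so this may apply. Use the new procedure for the remaining assignments and state who had access to the list until then.

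**Cost:** a short amendment and some EDC set-up. Randomisation falls on the treatment day, a small practical burden. No additional patients are needed.
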